## Abstract

**Background::**

The incidence of heart failure with normal ejection fraction (HFNEF) is increasing yearly, accounting for approximately half of all heart failure cases. Even after standardized treatment, the patient's prognosis is not good. Therefore, it is necessary to explore new treatment methods for HFNEF. Yangyin Shuxin Decoction, a traditional Chinese medicine prescription from our clinical experience in the treatment of HFNEF, has a potential cardioprotective effect. Preliminary clinical trials have shown that this prescription can improve the quality of life of HFNEF. This prompted us to use more objective indicators to further evaluate whether Yangyin Shuxin Decoction can improve the exercise capacity in HENEF patients.

**Methods::**

This is a single-center parallel randomized controlled trial. The 64 patients who met the inclusion criteria were from the Cardiovascular Clinic. They will be randomly assigned to the treatment group (Yangying Shuxin Decoction combined with standard treatment) or the control group (standard treatment) according to the ratio of 1:1. The course of treatment will be 2 weeks. Both groups were interviewed at the following time points: of at enrollment (V1), and week 2 (V2), week 4 (V3), week 8 (V4), and week 12 (V5) after enrollment. The primary indicator is the peak oxygen consumption (Peak VO2) of the cardiopulmonary exercise test (CPET). Secondary indicators include CPET indicators such as anaerobic threshold oxygen consumption, carbon dioxide ventilation equivalent slope, echocardiographic indicators such as the ratio of mitral peak velocity of early filling to early diastolic mitral annular velocity(E/e′), left atrial volume index (LAVI), left ventricular mass index (LVMI), the peak velocity of tricuspid regurgitation (TR), B-type natriuretic peptide (BNP), New York Heart Association (NYHA) cardiac function grading, and so on. These indicators will be used to evaluate the effect of Yangyin Shuxin Decoction on exercise capacity in patients with HFNEF.

**Discussion::**

At present, it is unclear whether the exercise capacity can be maintained after long-term use of Yangyin Shuxin Decoction. In this study, we will evaluate whether Yangyin Shuxin Decoction can improve the exercise capacity and quality of life of patients with HFNEF. This will provide an objective basis for the therapeutic effect of traditional Chinese medicine on HFNEF.

**Trial Registration::**

This study protocol has been listed in the Chinese Clinical Trial Registry (registration number: ChiCTR-IOR-17014206, http://www.chictr.org.cn/showproj.aspx?proj=24304) on December 28, 2017.

## Introduction

1

China gradually enters an aging society and the incidence of heart failure with normal ejection fraction (HFNEF) is increasing yearly.^[1]^ These patients account for approximately half of all patients with heart failure (HF).^[2–4]^ Beta-adrenergic receptor blockers, angiotensin-converting enzyme inhibitors (ACEI), angiotensin receptor blockers (ARB), and so on are routinely used to treat HFNEF. However, they have not improved the prognosis and reduced the mortality of patients with HFNEF.^[5–7]^ Patients with HFNEF who received conventional treatment still have problems, such as low exercise capacity and low quality of life.^[8]^ Previous clinical studies^[9–12]^ suggested that traditional Chinese medicine (TCM) had certain efficacy in relieving symptoms, increasing activity capacity, improving quality of life, and other aspects in patients with HFNEF. However, the quality of these studies is poor. Some deficiencies reduce the level of evidence such as large differences in the study population, unclear inclusion/exclusion criteria, non-uniform TCM syndromes, relatively single clinical evaluation indicators, and other problems.^[13]^

Yangyin Shuxin Decoction is a TCM prescription for treating HFNEF. It has the effects of nourishing Yin (Yangyin), promoting blood circulation (Huoxue), and clearing away heat (Qingre). Preliminary clinical trials have proved that it can improve the quality of life of patients with HFNEF.^[14]^ The single drug component of each drug in the prescription has multiple targets to improve the heart and lung functions and increase the exercise capacity. Hence, we planned to use more objective indicators to further evaluate whether Yinyin Shuxin can improve the exercise capacity of patients with HFNEF.

We hypothesized that Yangyin Shuxin Decoction could improve the exercise capacity of patients with HFNEF. Moreover, we designed this randomized controlled trial to compare the efficacy of conventional western medicine and Yangyin Shuxin Decoction combined with conventional western medicine on exercise capacity in patients with HFNEF. The relevant design principles and implementation schemes of the randomized controlled trial protocol are as follows (Fig. 1).

**Figure 1 F1:**
[figure not shown]
Study flow chart.

## Methods

2

### Study design

2.1

This is a single-center, prospective, parallel, and randomized controlled trial. Based on a computer-generated randomized number, 64 patients with HFNEF will be randomly assigned to either the treatment or control group. Patients in the treatment and control groups will be treated with a drug intervention for 2 weeks and followed up for 12 weeks. We will terminate this test when the following situations occur:

1.a serious safety incident occurred during the test;2.there are major errors in the clinical trial protocol;3.serious deviations occur so that it is difficult to evaluate the efficacy of the drug; and4.the project management department cancels the test.

A data monitoring committee will be established, mainly to make interim analysis and assess adverse events. The committee will review the core trial processes and documents, and discuss any amendments to the main study protocol. Any adverse event will be recorded in the CRF and reported to the data monitoring committee in a timely manner. We will provide appropriate compensation for any injured subjects. The Standard Protocol Items: Recommendations for Interventional Trials (SPIRIT) checklist is provided as Additional file 1.

### Participants

2.2

All of the 64 patients with HFNEF will be enrolled in the Department of Cardiology, the First Teaching Hospital of Tianjin University of TCM. First, the patients will be fully introduced to the benefits and risks of the treatment. Second, the patients need to sign the informed consent on a voluntary basis. Then, the patients will be divided into the treatment (Yangying Shuxin Decoction combined with the standard treatment) or control (standard treatment) groups according to the coding sequence from the pre-set random number table. The inclusion and exclusion criteria are shown in Table 1.

**Table 1 T1:**
[figure not shown]
Eligibility criteria.

The follow-up period was 12 weeks. A full physical examination and assessment of adverse events will be performed for all participants. After the patient signs the informed consent form, we will collect general information including demographics, medical history, and concomitant medications. Two clinical controls were performed at the time of enrollment (V1) and week 2 (V2). Indicators include cardiac ultrasound, CPET, BNP, NYHA cardiac function grading, EQ-5D-5L, TCM four-diagnostic information score, syndrome judgment, blood pressure, heart rate, weight, and so on. Blood and urine samples will also be taken. During the follow-up period, the investigator will contact the participants via telephone at weeks 4 (V3), 8 (V4), and 12 (V5) to monitor the patient's blood pressure, weight, NYHA cardiac function, hospitalization/outpatient costs, and compound endpoint events to assess the patients’ quality of life. This program was prepared in accordance with the standard protocol project SPIRIT 13. The specific process of the study is shown in Table 2.

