#### Primary outcome

2.4.1

The change of Peak VO2 in cardiopulmonary exercise test.

Secondary outcomes:

anaerobic threshold and ventilatory equivalent for carbon dioxide (VE/VCO2) slope detected in the cardiopulmonary exercise test.E/e′, LAVI, LVMI, and TR detected with ultrasonic cardiogram.BNP, NYHA cardiac function grading, EQ-5D-5L, TCM four-diagnostic information score, syndrome judgment, compound endpoint events, and so on.

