### Blinding

2.7

Blinding the researchers responsible for the implementation and patients included is not possible due to the particularity of dosage forms. The investigators are responsible for distributing the drugs. To ensure the reliability of the test, the personnel and statistical experts performing the outcome index evaluation will be blinded. All research team members were instructed not to communicate with the participants regarding their allocation.

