### Data collection and management

2.8

To assess the patients’ health status since the last visit and HFNEF-related re-hospitalization or unplanned medical conditions throughout the study period, the two groups will be contacted every 2 weeks or a month. All original data will be observed directly by clinical researchers and documented completely and timely in the case report form (CRF), including the reasons why patients cannot participate. To ensure the reliability of data, the CRF will be entered by the double-entry method. All errors will be crossed out and corrected and signed by the corresponding investigator. All these data will be locked in a separate cabinet. Only authorized investigators are permitted to access this information.

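### Section 2.2 gives the week 4, 8 and 12 telephone collection of NYHA class and compound endpoint events to the investigator role, which section 2.7 has distributing the drugs, while 2.7 promises blinded outcome evaluation

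*Protocol article*

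**What the plan says.** Section 2.7 (Blinding) makes three statements that bear on this point. On who cannot be blinded: "Blinding the researchers responsible for the implementation and patients included is not possible due to the particularity of dosage forms". On who dispenses: "The investigators are responsible for distributing the drugs". On outcome assessment: "the personnel and statistical experts performing the outcome index evaluation will be blinded". The last is not restricted to particular outcomes or visits. The section adds that "All research team members were instructed not to communicate with the participants regarding their allocation".

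Section 2.2 (Participants, text after Table 1) sets out the follow-up: "the investigator will contact the participants via telephone at weeks 4 (V3), 8 (V4), and 12 (V5"). Besides blood pressure and weight, the calls cover "NYHA cardiac function, hospitalization/outpatient costs, and compound endpoint events to assess the patients’ quality of life".

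Section 2.4.1 lists the last group of secondary outcomes as "BNP, NYHA cardiac function grading, EQ-5D-5L, TCM four-diagnostic information score, syndrome judgment, compound endpoint events, and so on". NYHA class and compound endpoint events are therefore both efficacy outcomes.

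Section 2.8 (Data collection and management) says of data capture in general: "All original data will be observed directly by clinical researchers and documented completely and timely in the case report form (CRF").

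**The concern.** The control arm receives conventional treatment without a placebo decoction (section 2.3), so anyone who hands out the decoction knows the arm. Patients know it too. In such a trial a blinded assessor is the main protection left for outcomes that involve judgement. NYHA class is one of these: over the telephone it depends on what the patient says and on how the caller turns that into a grade.

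The article uses one role name, investigator, both for dispensing and for the follow-up calls. A site following section 2.2 as written could have a person who dispensed the decoction grade NYHA class at weeks 4, 8 and 12 and still believe it complied with section 2.7. A between-group difference in NYHA class over that period would then be open to assessor bias. The clinic measurements could not settle the matter, because section 2.2 lists CPET, echocardiography and BNP at V1 and V2 only.

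**Working it through.** The point rests on no sample size or power figure, and the total of 64 patients plays no part in it. The check is a comparison of statements and a count of visits.

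**Step 1. Who is unblinded?** Section 2.7 names the implementing researchers and the patients as people who cannot be blinded, and has the investigators distribute the drugs. With no placebo in the control arm, dispensing reveals allocation. The investigator role, in its dispensing function, is therefore unblinded.

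**Step 2. Who is said to be blinded?** The same section promises blinding for the personnel evaluating outcomes and for the statisticians. It gives the personnel no other name and does not say which visits they attend.

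**Step 3. Who obtains the V3 to V5 outcomes?** Section 2.2 says the investigator, by telephone. Section 2.8, which has clinical researchers observe and record all original data, does not mention a separate blinded caller.

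**Step 4. Are these outcomes within the blinding promise?** NYHA class and compound endpoint events are on the secondary outcome list in section 2.4.1. The promise in 2.7 excludes no outcome, so it covers them.

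Steps 1 to 4 together: a role described as unblinded collects outcomes that are said to be evaluated blind. The conflict is between roles.

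**Step 5. How much is exposed?**

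| Outcome | V1 | V2 | V3 | V4 | V5 |
|---|---|---|---|---|---|
| Peak VO2 and other CPET indices | clinic | clinic | – | – | – |
| Echocardiography, BNP | clinic | clinic | – | – | – |
| EQ-5D-5L, TCM score, syndrome judgment | clinic | clinic | – | – | – |
| NYHA class | clinic | clinic | telephone | telephone | telephone |
| Compound endpoint events | – | – | telephone | telephone | telephone |

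The table follows the lists in the text of section 2.2. Table 2, the visit chart, is not legible in the copy reviewed. NYHA class has four post-baseline gradings (V2, V3, V4, V5), of which three (V3, V4, V5) are by telephone: 3/4 = 75%. Composite events are named only for the telephone contacts, but the article does not define the components, so the scope for caller judgement cannot be established.

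**Step 6. Does the instruction on allocation resolve it?** It restricts what staff say to participants. It does not blind a caller who has already handed out the decoction.

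**The case against.** The strongest reply is that the caller's identity is inferred. The article uses staff labels loosely (investigator, clinical researchers, implementing researchers, personnel), and section 2.7 itself separates those who implement from those who evaluate. Read in that light, the caller could be one of the blinded personnel. This stands in part: a reader might infer that the very person who hands out the decoction makes the calls, and no text says so. The conflict between roles remains, because the same label is attached to both tasks and nothing separates them.

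A second reply is that the calls only monitor, and that blinded personnel may evaluate what an unblinded caller writes down. That would be consistent with both sections, but the article describes no such step. For NYHA class it would also help little if the grade is formed during the call.

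A third reply is that staffing of calls and event adjudication are commonly left to the full protocol. That is correct, and the absence of such detail is not the point here. The point is that two statements the article does make do not fit together.

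A fourth reply is that patients are unblinded, so telephone NYHA class carries patient-report bias whoever calls. This stands. A blinded caller removes only the assessor's share of the bias.

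A reader might also infer that every event after week 2 is compromised. The documents do not support that: the composite is undefined, and a component such as hospitalization would leave a caller little room for judgement.

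**Conclusion.** Sections 2.2 and 2.7 conflict at the level of roles and should be reconciled. The conclusion assumes that investigator means the same role in both sections, which is the plain reading but is not stated.

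The exposure is mainly telephone NYHA class at three of the four post-baseline time points. Compound endpoint events may be affected to a degree that depends on their components. The primary outcome, Peak VO2, and the other outcomes listed only for V1 and V2 are untouched.

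A reader might go further and conclude that the blinding statement is untrue for the follow-up period, or that a week 4 to 12 NYHA difference would be nothing but assessor bias. Neither follows. The article does not show that one individual does both tasks, and it does not show that any bias occurs. Nor do the documents give a misgrading rate, so no number of misclassified patients can be derived from them.

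This is a moderate point: it concerns secondary outcomes, and it is cheap to correct.

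**What to change.** Amend section 2.2 so that the V3, V4 and V5 calls are made by the blinded outcome personnel promised in section 2.7, and state that the caller has not dispensed the decoction. Use the same call script in both arms, opening with a request that the patient not mention the treatment received. Have the caller record any unblinding, with the visit at which it happened.

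If this cannot be arranged, limit the blinding statement in 2.7 to the outcomes it covers and describe week 4 to 12 NYHA class as open-label in the protocol and the report.

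The first option reassigns calls to personnel the article already promises and adds a short script and one field on the case report form. It does not change the sample size, outcomes, visits or treatment. The second costs one sentence but leaves the assessor bias in place. Under either option some patients may still reveal their arm, and bias from unblinded patient report remains.

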**Table 2 T2:**
[figure not shown]
Research access flow chart.

### Interventions

2.3

Other TCM preparations are not allowed during the washout period for 2 weeks. The patients in the treatment group will be treated with conventional western medicine combined with Yangyin Shuxin Decoction 150 mL, twice a day. All Chinese herbal medicines in Yangyin Shuxin Decoction are from the Department of Pharmacy, the First Teaching Hospital of Tianjin University of TCM. The decocting room is uniformly fried and made into a vacuum package of 150 mL. The remaining decoction will be recycled if the participants withdraw from the test midway. The patients in the control group will receive conventional western medicine treatment. The duration will be 2 weeks. Both groups will be interviewed at the following time points: enrollment (V1), week 2 (V2), week 4 (V3), week 8 (V4), and week 12 (V5) after enrollment.

The TCM theory believes that patients with HFNEF have clinical syndrome characteristics of yin deficiency, blood stasis, and internal heat.^[15]^ Each of the single-drug ingredients in Yangyin Shuxin Decoction includes a variety of compounds such as polyphenols, terpenoids, saponins, and alkaloids that are beneficial to the cardiovascular system. The relevant bioactive ingredients and potential mechanisms are shown in Table 3. These ingredients have the combined effects of improving heart and lung functions, increasing activity tolerance, improving microcirculation, and improving immunity and body antioxidants in patients with HFNEF.

**Table 3 T3:**
[figure not shown]
Cardiovascular effects and potential mechanisms of active ingredients.

Western medicine standard treatment plan is implemented according to the “China Heart Failure Diagnosis and Treatment Guide 2014”^[32]^ and “2016 ESC Guidelines for the diagnosis and treatment of acute and chronic heart failure.”^[33]^ The Western medicine standard treatment includes health education for patients to help them establish a heart-healthy lifestyle (such as salt restriction, water restriction, weight monitoring, physical exercise, smoking cessation, alcohol withdrawal, and so on) and medication guidance and emergency management instructions. In addition, other TCMs for the treatment of cardiovascular diseases should be avoided.

### Outcomes

2.4

#### Primary outcome

2.4.1

The change of Peak VO2 in cardiopulmonary exercise test.

Secondary outcomes:

anaerobic threshold and ventilatory equivalent for carbon dioxide (VE/VCO2) slope detected in the cardiopulmonary exercise test.E/e′, LAVI, LVMI, and TR detected with ultrasonic cardiogram.BNP, NYHA cardiac function grading, EQ-5D-5L, TCM four-diagnostic information score, syndrome judgment, compound endpoint events, and so on.

#### Security outcomes

2.4.2

Vital signs, some laboratory tests, and adverse events are considered as safety outcomes. Vital signs, including blood pressure and heart rate, routine laboratory tests (routine urinalysis, routine blood test, and hepatic and renal functions), and electrocardiograms, and the adverse events will be documented at each visit.

### Patient and public involvement

2.5

The patients or the public were not involved in the design or in conducting, reporting, or disseminating our research.

### Sample size

2.6

The sample size is computed based on the literature “Effect of If-channel inhibition on hemodynamic status and exercise capacity in HF with preserved ejection fraction: a randomized trial,”^[34]^ peak VO2 on day 7 is 3.0 ± 3.6 mL/kg/min in the treatment group and 0.4 ± 2.7 mL/kg/min in the control group. Sixty-four patients will be recruited with a single-sided alpha of 0.05, a power (1 − *β*) of 0.90, and a dropout rate of 20%. The calculation formula is as follows^[35]^: 
[figure not shown]

### Blinding

2.7

Blinding the researchers responsible for the implementation and patients included is not possible due to the particularity of dosage forms. The investigators are responsible for distributing the drugs. To ensure the reliability of the test, the personnel and statistical experts performing the outcome index evaluation will be blinded. All research team members were instructed not to communicate with the participants regarding their allocation.

### Data collection and management

2.8

To assess the patients’ health status since the last visit and HFNEF-related re-hospitalization or unplanned medical conditions throughout the study period, the two groups will be contacted every 2 weeks or a month. All original data will be observed directly by clinical researchers and documented completely and timely in the case report form (CRF), including the reasons why patients cannot participate. To ensure the reliability of data, the CRF will be entered by the double-entry method. All errors will be crossed out and corrected and signed by the corresponding investigator. All these data will be locked in a separate cabinet. Only authorized investigators are permitted to access this information.

### Statistical analysis

2.9

SPSS23.0 statistical analysis software will be used to calculate the test data, and descriptive statistics will be conducted for all the data. For the differences between the test groups, chi-square test will be used for the counting data. The *t* test will be applied when normality (and homogeneity of variance assumptions) is satisfied, otherwise the rank sum test will be used.

The number of screened patients and reasons for exclusion will be reported, as well as protocol violations and reasons. An effectiveness analysis will be conducted using the randomized populations. Participants who have received treatment but there is no valid evaluation data will be considered as missing and will be included in the effectiveness analysis.

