In addition, during the follow-up period of 3 months, patients’ clinical conditions, especially regarding the re-hospitalization rate and the outpatient and inpatient costs will be tracked to comprehensively evaluate the patients’ exercise capacity and quality of life. At present, it is unclear whether the exercise capacity can be maintained after the long-term use of Yangyin Shuxin Decoction. Even so, this study will provide valid data for TCM to improve the exercise capacity of patients with HFNEF. Although it cannot fully explain the multi-linked interventional and pharmacological mechanism of TCM decoction on HFNEF, we can still use it as an intervention method and explore the mechanism from the perspective of pathophysiology in the future, because the fact that it can improve exercise tolerance in patients with HFNEF has been proven.

In conclusion, this is a single-center parallel randomized controlled trial. We will evaluate whether Yangyin Shuxin Decoction can improve the exercise capacity and quality of life of patients with HFNEF. This will provide an objective evidence for the therapeutic effect of TCM on HFNEF.

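### Event outcomes followed to week 12 fall under a chi-square rule that cannot use partial follow-up; time to first event with censoring would be a cheap improvement

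*Protocol article*

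**What the plan says.** Section 2.4.1 ends its list of secondary outcomes with "TCM four-diagnostic information score, syndrome judgment, compound endpoint events, and so on". Section 2.2 sets the length of observation ("The follow-up period was 12 weeks") and has compound endpoint events collected by telephone at weeks 4, 8 and 12. Section 2.8 has both groups contacted to assess "HFNEF-related re-hospitalization or unplanned medical conditions throughout the study period". The Discussion says of the patients' clinical course over three months: "especially regarding the re-hospitalization rate and the outpatient and inpatient costs will be tracked".

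For the comparison, section 2.9 states: "chi-square test will be used for the counting data". The t test and the rank sum test cover the other data. No method that uses follow-up time is named. The effectiveness analysis uses the randomised population, and section 2.9 adds: "Participants who have received treatment but there is no valid evaluation data will be considered as missing and will be included in the effectiveness analysis".

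Section 2.6 allows for "a dropout rate of 20"%, in the calculation for peak VO2. It gives no split by arm and no time point.

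**The concern.** A chi-square test needs every patient classed as event or no event at week 12. A patient last reached at week 4 without an event has four weeks of information and no week-12 status. To keep that patient, as section 2.9 seems to intend, someone must assign a status. To leave the patient out is to discard the four weeks. Either step is an extra assumption, and the result can depend on which is chosen.

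Loss could differ by arm. Patients and treating staff know the allocation (section 2.7), the last visit with clinical tests is at week 2, and later contact is by telephone (section 2.2). A single week-12 proportion also pools events from the 2 treatment weeks with those from the following 10 weeks.

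**Working it through.** **The plan's own figure.** The sample size rests on peak VO2: difference 3.0 − 0.4 = 2.6, variance (3.6² + 2.7²)/2 = 10.125, one-sided alpha 0.05, power 0.90. Then n per arm = 2 × 10.125 × (1.645 + 1.282)²/2.6² = 25.65, and 2 × 25.65/0.8 = 64.1. The stated 64 is reproduced. The 20% therefore belongs to this calculation, and nothing below changes N.

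**Assumptions for the check; the document gives none of these values.** True 12-week risk p is the same in both arms, 10 to 25%. The hazard is constant: R(t) = 1 − exp(−λt), with R(12) = p. Loss is unrelated to event risk, q = 10% in one arm and 30% in the other (20% on average).

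**Loss patterns.** (i) All at week 2. (ii) Uniform over weeks 2 to 12. (iii) Constant rate over the 12 weeks.

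**Formulas.** For (i) and (ii), risk with losses counted as event-free = (1 − q)p + qR_L, where R_L is the risk up to loss (averaged over loss times in (ii)). If event-free losses leave the denominator, divide by 1 − q(1 − R_L). For (iii), with λ = −ln(1 − p) and c = −ln(1 − q) over the whole period, observed risk = λ/(λ + c) × [1 − exp(−(λ + c))]. The share lost event-free is the same expression with c on top.

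**Numbers at p = 10%.** R_L is 0.0174 in (i) and 0.0593 in (ii).

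- (i), event-free: 0.9 × 0.10 + 0.1 × 0.0174 = 0.0917, and 0.7 × 0.10 + 0.3 × 0.0174 = 0.0752.
- (i), removed: 0.0917/(1 − 0.1 × 0.9826) = 0.1017, and 0.0752/(1 − 0.3 × 0.9826) = 0.1067.
- (iii), event-free: 0.1054/0.2107 × 0.19 = 0.0950, and 0.1054/0.4620 × 0.37 = 0.0844.
- (iii), removed: 0.0950/(1 − 0.0950) = 0.1050, and 0.0844/(1 − 0.2856) = 0.1181.

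| Loss pattern | Losses event-free: 10% arm, 30% arm | Ratio | Event-free losses removed: 10% arm, 30% arm | Ratio |
|---|---|---|---|---|
| (i) week 2 | 9.17%, 7.52% | 0.820 | 10.17%, 10.67% | 1.048 |
| (ii) uniform | 9.59%, 8.78% | 0.915 | 10.59%, 12.23% | 1.155 |
| (iii) constant rate | 9.50%, 8.44% | 0.888 | 10.50%, 11.81% | 1.125 |

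For risks of 10 to 25%, the event-free rule gives 0.82 to 0.92 across the three patterns. Removing event-free losses gives 1.10 to 1.13 in pattern (iii), and 1.04 to 1.16 once (i) and (ii) are added. The direction reverses with the rule. Dropping every lost patient, including those who had an event before loss, gives a ratio of 1.00 in this model but throws away recorded events and follow-up.

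**Equal loss, 20% in both arms.** The ratio is 1.00 under either rule. The level is not right: at p = 15% the event-free rule shows 0.8 × 0.15 + 0.2 × 0.0267 = 12.5% in (i) and 0.8 × 0.15 + 0.2 × 0.0898 = 13.8% in (ii).

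**Effect on the test.** With 32 per arm, losses counted as event-free and pattern (iii), the simulated error of a two-sided 5% chi-square test at risks of 10 to 30% is 5.6 to 6.0% with 10% against 30% loss, and 5.2 to 5.4% with equal loss. At 10% risk about 3 events per arm are expected (32 × 0.095 = 3.0 and 32 × 0.084 = 2.7).

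**The case against.** A reader might infer that the arm losing more patients will look better. The document does not support that. It needs two conditions together, unequal loss and lost patients counted as event-free, and the text states neither. Section 2.9 calls patients without valid data missing, which does not suggest event-free, and removing event-free losses turns the ratio the other way. A reader might also infer that at least 20% will be lost by week 12. That does not follow: the 20% is for peak VO2, which needs an exercise test, and a patient who misses that test may still answer the telephone.

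A chi-square test is also defensible here. Follow-up is short and the same for everyone, so there is no staggered entry to handle, and with near-complete contact a 12-week proportion is adequate. Section 2.9 is a short general rule that does not name the event outcomes, re-hospitalisation is not itself listed in section 2.4, and a full analysis plan may say more. Finally, censoring assumes uninformative loss, which may be doubtful in an open trial, and one log-rank test does not separate on-treatment from later events.

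Most of this stands, and it limits the point. What remains is that the only stated rule for yes/no outcomes, combined with the instruction to include patients without valid data, cannot be applied to a patient lost before week 12 without an unstated assumption about status.

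**Conclusion.** The point holds as a mismatch between the stated test and outcomes observed over time. It is not a demonstrated bias. With an assumed 10% against 30% loss and equal true risks, the apparent ratio is about 0.82 to 0.92 under one handling of losses and about 1.10 to 1.13 under another (1.04 to 1.16 if the pattern of loss is also varied). With equal loss there is no bias between arms, and only the level of risk is off. The sizes rest on assumed event risks, a constant hazard and loss unrelated to risk. The outcome is secondary, events will be few, the rise in test error is about half a percentage point, and the primary analysis and N = 64 are untouched. Low priority: a cheap improvement.

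**What to change.** In section 2.9, take compound endpoint events and re-hospitalisation out of the chi-square rule. Analyse time from randomisation to first event, with Kaplan-Meier 12-week risks by arm, a confidence interval for their difference and a log-rank test, censoring at last contact. Report the number lost by arm and when. The Kaplan-Meier curves also show when events fall, though the log-rank test does not test this. Keep chi-square for outcomes recorded once. If the sponsor prefers a 12-week proportion, section 2.9 should at least say how a patient lost before week 12 is classified.

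The cost is a few lines of text and two CRF fields, date of first event and date of last contact; the contacts are already scheduled. Censoring assumes uninformative loss, and with few events the interval will be wide under either method.
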